### Data collection, processing, and analysis procedures

#### Data collection instrument

A specific form will be developed for the study. It will be in the form of a handwritten log. Prospective data collection will be performed on the day of the intervention and subsequently for the data following the intervention. The follow-up items for the participants are presented in Table 1 and Fig. 2.

**Table 1 Tab1:** The standard protocol items and timing of the measurements

Measurements	T0	T1	T2	T3
Age, BMI, complaints, gynecological and obstetric history	x			
The largest cyst diameter	x			
Side of pathology	x			
Surgery: duration, blood loss, perioperative complications, ASRM classification	x			
Hemoglobin	x			
Bipolar coagulation (number of points coagulated)	x			
Suture (number of stitches sutured)	x			
Hemostatic (number of hemostatic used)	x			
AMH	x	x	x	x
AFC in affected ovary	x	x	x	x
AFC in the contralateral ovary	x	x	x	x
Total AFC	x	x	x	x

*BMI* body mass index, *T0* before surgery, *T1* one month after surgery, *T2* three months after surgery, *T3* six months after surgery

**Fig. 2 Fig2:**
[figure not shown]
Follow-up items for the participants. Recommendations for Interventional Trials (SPIRIT) figure

#### Data processing and analysis

The data will be double-entered by two different data entry operators, using the Epi Info software program, version 7.2. The two databases will be compared using the Validate function of the Epi Info software program. Statistical analysis will be conducted using the Microsoft Excel software and the SPSS statistical software package for Windows, version 19.0.0. The data entry operators and the statistician will be blinded in that they will receive the data marked simply as A, B, or C and will be unaware of which procedure corresponds to which letter. A significance level of 5% will be determined for all the statistical tests.

To analyze the numerical variables AMH and AFC, the Kolmogorov–Smirnov test of normality will be used to determine the type of analysis to be performed. If distribution is normal, two-way analysis of variance (ANOVA) will be used, with the group representing an independent factor (bipolar energy × suture × hemostatic matrix). Another factor to be analyzed will be paired time points (before surgery × 1 month × 3 months × 6 months). If distribution is not normal, non-parametric tests will be used to analyze the variables.

The Kruskal–Wallis test will be used to compare variables between the three groups at each time point, with Tukey’s multiple comparison test being used when comparisons are statistically significant. The Friedman test will be used to perform intra-group comparisons at the four evaluation moments, with Tukey’s multiple comparison test being used when they are significant.

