### Study design

An open-label RCT will be performed to compare the impact of hemostatic techniques (bipolar coagulation versus laparoscopic suture versus hemostatic matrix) during laparoscopic surgery for an ovarian endometrioma on the ovarian follicular reserve.

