### Participant selection and randomization

Eligible patients will be invited to participate in the study and those who accept the invitation will be admitted.

The sample will be divided into three groups according to the hemostatic technique used:Bipolar coagulation (bipolar Maryland, ref.702505ML, Astus Medical©, Copyright 2015, Tampa, FL, USA) with 30-W power and a Valleylab generator (Medronic©, Copyright 2017, Medtronic Parkway, Minneapolis, MN, USA). The number of coagulated points will be counted; the time for coagulation will be measured in seconds.Laparoscopic suturing with simple suture (2–0/Vicrylpolyglactin absorbable synthetic suture; Ethicon Inc., NJ, USA). The number of sutures will be recorded.Hemostatic matrix (Surgicel® Original Absorbable Hemostat, Ethicon, USA).

Randomization to receive the various hemostatic techniques (bipolar coagulation, laparoscopic suture, or hemostatic matrix) during laparoscopic surgery for endometrioma will be performed based on a list of sequential numbers generated using the Random Allocation software package, version 2.0. The list will consist of numbers in the range of 1–84 (the total number of participants to be randomized) and the letters A, B, and C, which will designate the study groups. An individual not directly involved in the study will prepare opaque envelopes numbered 1–84, which will contain the group to which the patient must be allocated.

At the time of inclusion, a number will be assigned to each participant, corresponding to her order of entry in the study. During surgery, at the time of hemostasis, a nurse at the surgical theater will open the envelope containing the corresponding number. Thus, allocation will remain concealed up to that specific moment during surgery, since it is impossible to blind the surgeon to the technique to be used.

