### Procedures for the assessment of ovarian reserve

Ovarian reserve will be assessed by measuring AMH and by performing AFC using ultrasonography at four different moments: before surgery and one, three, and six months after surgery. Serum samples will be obtained from each participant and centrifuged for 10 min to separate the cell contents and debris. Each serum sample will be transferred to polypropylene tubes and stored at − 80 °C.

AMH levels will be quantitatively measured using enzyme-linked immunosorbent assay (ELISA) (Diagnostic Systems Laboratories, Webster, TX, USA), with a detection sensitivity of 0.006 ng/mL.

Transvaginal ultrasonography for antral follicle count will be performed during the early proliferative stage (days 3–7 of the menstrual cycle) and the total number of follicles with diameters < 10 mm will be considered.

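### The A/B/C masking of data entry and statistician does not hold while technique-specific fields travel with the letters, and the AFC reader is not among the roles stated to be blinded

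*Protocol article*

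**What the plan says.** Study design declares the trial open: "An open-label RCT will be performed to compare the impact of hemostatic techniques". Participant selection and randomization explains that the allocation envelope is opened in theater at the moment of hemostasis, "since it is impossible to blind the surgeon to the technique to be used".

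Data processing and analysis names two masked roles: "The data entry operators and the statistician will be blinded in that they will receive the data marked simply as A, B, or C". The stated aim is that they "will be unaware of which procedure corresponds to which letter". No other role is said to be masked.

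Table 1, under Data collection instrument, lists among the recorded items "Bipolar coagulation (number of points coagulated" and "Suture (number of stitches sutured", in each case as a count, plus a count of hemostats used. Participant selection and randomization adds coagulation time in seconds.

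For the outcomes, Procedures for the assessment of ovarian reserve says "Transvaginal ultrasonography for antral follicle count will be performed during the early proliferative stage" and "AMH levels will be quantitatively measured using enzyme-linked immunosorbent assay (ELISA". It does not say who performs the scan or what that person knows.

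**The concern.** There are two separate problems.

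First, the article claims a protection and also specifies data that defeat it. A group letter conceals the arm only if nothing else in the record reveals it, and here three recorded items do. The trial could then report a blinded analysis that its own data form contradicts, and readers would give that analysis credit it has not earned.

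Second, masking matters most where judgement enters the measurement. AFC depends on the person who counts the follicles. The Discussion records the investigators' belief that bipolar energy may affect ovarian function. A reader who shares that belief and knows the technique could, without intending to, count lower in the bipolar arm. That would bias the comparison the trial was set up to make.

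**Working it through.** The plan gives no figure on this point, so the check sets its statements side by side.

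**Step 1. Does each technique-specific item point to one arm?**

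| Item recorded | Arm it applies to | Where stated |
|---|---|---|
| Points coagulated | Bipolar | Table 1; Participant selection and randomization; Procedures for laparoscopic surgery |
| Coagulation time | Bipolar | Participant selection and randomization; Procedures for laparoscopic surgery |
| Stitches | Suture | Table 1; Participant selection and randomization; Procedures for laparoscopic surgery |
| Hemostats used | Matrix | Table 1 |

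There are three arms, and each has at least one item of its own.

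**Step 2. Do these items reach the masked roles?** Data collection instrument describes a single study form kept as a handwritten log. Data processing and analysis has the data entered twice, by two operators. The Discussion says that the number of coagulated points will be summarized descriptively, so that item has to be entered and has to reach whoever does the analysis. Nothing describes a separate sheet, a separate file or a delayed release.

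**Step 3. What can be decoded?** The letter whose records carry coagulation counts is bipolar, and the letter whose records carry stitch counts is suture. The third letter is then the matrix by elimination. The letters are fixed for the whole trial, so decoding one letter reveals the technique for every woman in that arm (84 / 3 = 28 planned per arm).

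**Step 4. Which outcomes are exposed to the reader?**

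- AFC is an ultrasound count of follicles below 10 mm, made before surgery and at 1, 3 and 6 months. The first count precedes the opening of the envelope, so it cannot be influenced by knowledge of the allocation. The three later counts can be.
- AMH is measured by ELISA on stored serum, which leaves little room for a reader's expectation. It is also the outcome on which the sample size rests.

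**Step 5. Is masking the AFC reader ruled out?** Impossibility of blinding is stated for the surgeon only. Procedures for laparoscopic surgery describes one set of port sites, with no difference between arms, so the document gives no reason why the reader could not be masked.

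**The case against.** The strongest reply is that a condensed article need not list every masked role. The blinding sentence sits in a section on data processing and describes how two roles receive data; leaving out the AFC reader does not show that the reader knows the arm. That is right as far as it goes. A reader might infer that AFC is in fact read with knowledge of the technique, but the document does not say so. What stands is narrower: the trial is called open-label without qualification, blinded roles are named, and the AFC reader is not one of them.

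On the letters, Table 1 lists items and times. It is not a form layout or a database design, and the form is still described as something to be developed. The coagulation counts could be analyzed in a separate file. A reader might therefore go too far in calling the unmasking certain from the first completed record; a single form could also be ambiguous, for example if a woman in the bipolar arm needed no coagulation. What stands is that, on the plain reading, the fields and the letters go to the same people, and nothing in the text separates them.

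Three further points limit the consequence, and all are accepted:

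- The choice between ANOVA and non-parametric tests follows a named Kolmogorov–Smirnov test, and the fallback tests are named. Knowing the meaning of the letters does not change that test's result, so the point should not be tied to that branch.
- Double entry with a comparison of the two databases limits biased transcription.
- AFC appears as three of the four repeated reserve measures in Table 1, but these are affected-ovary, contralateral and total counts from the same ultrasound assessment. AFC is better described as one of two measures.

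**Conclusion.** The point holds in two parts of unequal strength.

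The masking of operators and statistician, as stated, is contradicted by the data they are to handle. This is an inconsistency within the document. It rests on one assumption, which is the plain reading: that the technique-specific fields are entered and passed on together with the letters.

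The AFC part is an inference from an unqualified open-label declaration and from the roles that are named as blinded. It supports saying that AFC is open to observer bias after surgery. It does not support saying that such bias has occurred, and it does not carry over to AMH in any important degree.

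Neither part can be given a size: the document contains no figure on reader variability or on the effect of unmasking. No sample size, test or significance level changes. This is a change that should be made because it is cheap and makes the blinding statement true; it does not threaten the trial as a whole.

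**What to change.** **1. Technique-specific fields.** Record points coagulated, seconds per point, stitches and hemostats on a separate sheet and in a separate file. Keep both from the operators and the statistician who handle the A/B/C outcome data, and link them only after the AMH and AFC analysis is locked. If this is not done, withdraw the statement that these roles are blinded.

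**2. Records already entered.** The Trial status section reports 32 women randomized by 24 April 2019, which leaves 84 − 32 = 52 to come. The document does not say how many records had been entered. Splitting the form cannot restore masking for those that were, so disclose that they may have been unmasked. If any were entered with their letters, an outcome file with fresh letters would still help a statistician who has not yet seen the data.

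**3. AFC reader.** State that the existing reader, who should not be the operating surgeon, is masked to allocation and to the operative notes, and that scan requests carry the study number only. If this is not feasible, report AFC as an unblinded outcome.

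The cost is a split form, a second file and a line on the scan request. Someone other than the masked operators has to enter the separate sheet, and if the surgeon currently does the scans, another reader is needed. Interventions, visits and tests are unchanged.

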Another point that has to be taken into consideration is that when endometriomas are compared to cysts of other types, AMH levels seem to be lower in the case of endometriomas even before surgery [27–35]. After surgery, there appears to be a similar decrease, irrespective of the etiology of the cyst [45–47]; however, this decrease is temporary, with a tendency to recover over subsequent months [39, 48–52].

In view of these considerations, the objective of the present study is to evaluate the effect on ovarian function of three different methods of hemostasis (bipolar coagulation versus suture versus hemostatic agents) in patients submitted to oophoroplasty because of an endometrioma, with ovarian function being assessed by measuring AMH and by performing AFC. The use of bipolar energy will be described in detail, including the number of points coagulated during the procedure. To the best of our knowledge, no other study has been conducted to evaluate the three different methods in the same clinical trial.

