### Sample size

Sample size was calculated using resources available at the Laboratory of Epidemiology and Statistics (LEE) website of the Dante Pazzanese Institute (http://www.lee.dante.br/pesquisa/amostragem/qua_2_medias.html). The calculation was based on data provided by Sönmezer et al. [48]. In that article, Sönmezer et al. detected a significant difference in the serum levels of AMH in the first month after surgery, with a measurement of 2.72 ± 1.49 for the patients who received the hemostatic matrix versus 1.64 ± 0.93 for the patients who received bipolar coagulation. Here, we assume that the standard deviation in the AMH measurement of 1.49 in the first month was significant, since that was the number that generated the largest sample size when compared with other values from that article. The difference to be detected is 1.08, which corresponds to the mean difference in AMH in the first month between the patients who receive hemostatic matrix and those who receive bipolar coagulation. On those grounds, and for a statistical power of 80% (*p* = 0.05), each group would have to have 23 participants. Considering possible losses, the sample will be increased by 20% to 28 participants per group, making a total of 84 women. It should be noted that the present sample maybe not detect a powerful difference in treatment arms, but relevant contributions are expected.

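### Every test is run at 5% with no primary outcome or visit named, so on the non-parametric path a false between-group finding is roughly 14–25% likely (six tests) or 19–37% (twelve), under assumed correlations

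*Protocol article*

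**What the plan says.** Under Data processing and analysis the protocol article sets one rule for error: "A significance level of 5% will be determined for all the statistical tests". The outcomes enter together and unranked: "To analyze the numerical variables AMH and AFC, the Kolmogorov–Smirnov test of normality will be used" to choose between two branches.

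- **Normal branch:** "If distribution is normal, two-way analysis of variance (ANOVA) will be used, with the group representing an independent factor", with visit as the second, paired factor.
- **Non-normal branch:** "The Kruskal–Wallis test will be used to compare variables between the three groups at each time point". Group pairs are then examined only after a significant overall result, "with Tukey’s multiple comparison test being used when comparisons are statistically significant". Friedman tests follow within each group.

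Table 1 (Data collection instrument) schedules AMH and three follicle counts at baseline and at one, three and six months: "AFC in affected ovary", the contralateral ovary, and the total.

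The Sample size section uses one quantity only. It relies on a cited trial that "detected a significant difference in the serum levels of AMH in the first month after surgery", and takes from it a matrix-versus-bipolar difference of 1.08 and an SD of 1.49. Neither that section nor any other calls this comparison primary.

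The Discussion says the results may guide surgeons towards the least damaging method. If no significant differences are found, they may choose by convenience and availability.

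**The concern.** The design is built on one comparison and the analysis is not tied to it. AMH and AFC have equal standing, all visits have equal standing, and each test has its own 5%. Tukey's procedure deals with the three group pairs inside one test. It does nothing across outcomes or visits.

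Because the Discussion's practical message turns on whether significant differences exist, one significant result on any measure at any visit is enough to move the reader from choosing by convenience to choosing a technique. The Background adds to the difficulty. It reports that studies disagree on AMH versus AFC, and it says of the postoperative fall in AMH that "this decrease is temporary, with a tendency to recover over subsequent months". Results that differ between visits or between measures are therefore plausible, and the plan does not say which one answers the trial's question about bipolar energy.

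**Working it through.** **1. The plan's own sample size.** Inputs (Sample size section): difference 1.08, SD 1.49, power 80%, 5%, sidedness not stated. Formula: n per group = 2 × [SD × (z for alpha + z for power) / difference]².

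- One-sided 5%: 2 × [1.49 × (1.645 + 0.842) / 1.08]² = 23.5, so 24 after rounding up. The stated 23 is approximately this.
- Two-sided 5%: 2 × [1.49 × (1.960 + 0.842) / 1.08]² = 29.9, so 30. This does not give 23.
- Two-sided power at 23 per group: 1.08 / (1.49 × √(2/23)) = 2.458; 2.458 − 1.960 = 0.498; power about 69% (normal approximation).
- Inflation: 23 × 1.2 = 27.6, so 28 per group, and 28 × 3 = 84, as stated.

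**2. Number of tests on the non-normal branch.** Only postoperative between-group tests are counted. Baseline tests cannot show an effect of technique, and the Friedman tests do not compare techniques.

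- AMH and one AFC measure × 3 visits = 6.
- AMH and all three AFC measures × 3 visits = 12. The analysis section says only AFC; testing all three is inferred from Table 1.

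**3. Chance of at least one false positive if independent:** 1 − 0.95^k.

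- k = 6: 1 − 0.95^6 = 26.5%.
- k = 12: 1 − 0.95^12 = 46.0%. This cannot apply if total AFC is the sum of the two ovaries, because the tests are then linked by construction.

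**4. Allowing for dependence.** The documents give no correlations, so these are assumed. There were 20,000 simulated null trials per setting, with 28 per group, normally distributed data, Kruskal–Wallis at 5%, and total AFC = affected + contralateral. The six-test column uses AMH and total AFC.

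| Correlation between visits | Correlation between outcomes | AMH, month 1 only | AMH, 3 visits | 6 tests | 12 tests |
|---|---|---|---|---|---|
| 0 | 0 | 4.6% | 14.0% | 25.6% | 40.2% |
| 0.3 | 0.3 | 5.0% | 13.8% | 24.7% | 37.1% |
| 0.5 | 0.3 | 5.1% | 12.6% | 23.2% | 34.7% |
| 0.7 | 0.5 | 4.9% | 11.1% | 19.2% | 27.7% |
| 0.8 | 0.5 | 4.7% | 9.8% | 17.0% | 25.3% |
| 0.9 | 0.7 | 4.8% | 8.4% | 13.6% | 19.0% |

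From the second row down, six tests give 14–25% and twelve give 19–37%. Naming AMH without naming a visit still leaves 8–14%. Only one outcome at one visit holds 5%.

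**5. ANOVA branch.** There is one model per outcome, not one test per visit. If independent:

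- Interaction test only, 2 to 4 outcomes: 1 − 0.95² = 9.8% to 1 − 0.95⁴ = 18.5%.
- Group and interaction tests, 4 to 8 in all: 18.5% to 1 − 0.95⁸ = 33.7%.

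**The case against.** **The article condenses a fuller protocol, and testing hierarchies commonly sit in an analysis plan.** This limits the point but does not remove it. The article is not merely silent: it states a 5% rule for all tests, prescribes comparisons at each visit, and describes a conclusion that turns on significance. If an unseen document already names a primary comparison, the remedy is only to bring it into this text.

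**An anchor exists.** The Sample size section fixes the outcome, visit, contrast and difference, so what is missing is close to a label. This stands in part, and it is why the fix is cheap. The analysis section, however, never refers back to that comparison.

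**The number of tests is uncertain.** This stands. Visit-by-visit testing belongs only to the Kruskal–Wallis branch. Table 1 is a measurement schedule, not a list of tests, so six tests is the more cautious count and twelve an inference.

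**Stronger readings a reader might reach.** One could infer a 46% false-positive chance from twelve independent tests, or a higher figure by adding baseline. The documents support neither. Total AFC, read as the sum of two other measures, rules out independence, and a baseline difference is chance imbalance that cannot be credited to a technique. Nor do the documents suggest that anyone intends to select a favourable result. The point is only that the plan as written would not prevent it.

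**Conclusion.** The concern holds in this limited form: the plan applies 5% to every test on unranked outcomes and visits, while sizing the trial on one comparison and basing its message on whether significant differences are found. In every setting tried, the chance of at least one false between-group finding after surgery exceeds 5%.

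The size depends on the branch and the count. The six-test independence figure of 26% is the ceiling when the measures are positively related. The correlated ranges in the working rest on correlations that the documents do not give. The twelve-test figures also rest on all three AFC measures being tested, with a ceiling of about 40% when the only dependence is the sum for total AFC. The ANOVA range of about 10–34% assumes independence and depends on which model terms count as evidence of an effect.

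**What to change.** In Data processing and analysis, state that AMH at one month, matrix versus bipolar, is the single primary comparison, tested at 5% whichever branch the normality test selects. This is the comparison the Sample size section already uses, and a single test returns the error for the main claim to 5%.

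State its sidedness. The 23 per group fits approximately only a one-sided 5% test. If the test is two-sided, restate the power.

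Treat all other outcomes, visits and contrasts, including those with suture, as secondary. Report them with estimates and confidence intervals, and say that none is sufficient alone to claim that technique matters. Word the Discussion's conclusion to match.

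The cost is a paragraph of text, with no new data or patients. The price is that some secondary results become supportive only, including the six-month results and the suture contrasts, although the objective covers three methods. The change should be fixed before the group codes are unblinded. At the time of the article 32 of 84 women had been randomized, and the statistician is to receive groups labelled only A, B and C, so this is feasible.

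### A normality test alone sends AMH to a common-variance ANOVA, although the plan's own figures suggest that the spread rises with the mean, so pairwise standard errors can be too small or too large

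*Protocol article*

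**What the plan says.** Under Data processing and analysis, the protocol article makes a Kolmogorov–Smirnov normality test the only gate for AMH and AFC. If it passes, "If distribution is normal, two-way analysis of variance (ANOVA) will be used", with group and time point as factors. If it fails, Kruskal–Wallis and Friedman tests are used. Tukey's multiple comparison is named, but only in the paragraph on those non-parametric tests. No check of equal variances, no transformation and no unequal-variance method is named.

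Under Sample size, the planning data come from one cited study at month 1: "2.72 ± 1.49 for the patients who received the hemostatic matrix versus 1.64 ± 0.93 for the patients who received bipolar coagulation". The text adds that "The difference to be detected is 1.08", applies the single SD of 1.49 to all arms, and concludes that "each group would have to have 23 participants". No AMH figures are given for the suture arm.

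**The concern.** ANOVA pools one error variance over the three arms and uses it for every comparison. A normality test says nothing about whether that is justified. In the plan's own figures the arm with the higher mean also has the higher SD, almost in proportion. If that pattern holds in this trial, a pooled variance is too small for a comparison of two high-AMH arms and too large for a comparison of two low-AMH arms.

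The protocol's Discussion section draws conclusions at the level of pairs: whether bipolar energy is to blame, and whether surgeons may pick the most convenient method if no differences are found. Those conclusions rest on the pairwise intervals and p-values, which an overall F test does not protect.

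**Working it through.** **Inputs.** From Sample size: matrix mean 2.72, SD 1.49; bipolar mean 1.64, SD 0.93; difference 1.08; 23 per arm, 28 after losses. Assumed, because the protocol gives nothing: suture equal to bipolar (1.64, SD 0.93), midway (2.18, SD 1.21), or equal to matrix (2.72, SD 1.49).

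**The plan's own figure.** n = 2 × [1.49 × (z for alpha + z for power) / 1.08]². One-sided 5% and 80% power give 23.5, which is close to the stated 23. Two-sided 5% gives 29.9, so 30. Losses: 23 × 1.2 = 27.6, so 28. The sidedness of the 23 is a separate matter and is not used below.

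**Does the spread follow the mean?**
- CV: 1.49/2.72 = 0.548; 0.93/1.64 = 0.567.
- SD ratio: 1.49/0.93 = 1.60; mean ratio: 2.72/1.64 = 1.66.
- Variance ratio: 1.60² ≈ 2.57.
- Log-scale SD if lognormal, √ln(1 + CV²): 0.512 and 0.528, almost equal.

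**Pooled against true standard error.** With equal arms, pooled SD = √(mean of the three variances). The ratio for a pair is pooled SD / √(mean of that pair's two variances); n cancels.
- Suture = bipolar: pooled SD = √[(1.49² + 0.93² + 0.93²)/3] = 1.147. Bipolar–suture: 1.147/0.93 = 1.23.
- Suture = matrix: pooled SD = √[(1.49² + 1.49² + 0.93²)/3] = 1.330. Matrix–suture: 1.330/1.49 = 0.89.

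| Suture assumed | Matrix–bipolar | Matrix–suture | Bipolar–suture |
|---|---|---|---|
| equal to bipolar | 0.92 | 0.92 | 1.23 |
| midway | 0.99 | 0.91 | 1.14 |
| equal to matrix | 1.07 | 0.89 | 1.07 |

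**Consequences, by simulation** (40,000 trials per case; 23 and 28 per arm; lognormal, gamma and normal data with the means and SDs above; month 1 only, because no within-patient correlation is given).
- Coverage of nominal 95% intervals: 92–93% where the standard error is clearly too small, 96–98% where it is too large.
- Unadjusted 5% error for a truly equal pair: about 8% if suture = matrix, about 1.8% if suture = bipolar, under all three distributions.
- The same pairs with Tukey's test: about 3.4% (3.1–3.8%) and about 0.5%, against a nominal per-pair level of about 2%.
- Overall F test with all arms equal: 4.5–5.1%.
- Unadjusted error after a change of method: 4.4–5.5% on the log scale (lognormal and gamma data); 4.4–5.1% with Welch comparisons on the raw scale (all three distributions).

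**Power of the three-arm F test at 23 per arm** (suture = bipolar / = matrix / midway).
- Lognormal: raw 90.2 / 86.3 / 77.5%; log 93.4 / 93.2 / 84.6%. The log scale gains about 3–7 points.
- Gamma: raw 89.3 / 85.8 / 75.7%; log 84.2 / 85.1 / 73.0%. The log scale loses about 1–5 points.

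**How often the ANOVA branch is reached.** With lognormal data, all three arms pass an uncorrected Kolmogorov–Smirnov test in 89–93% of trials, and the Lilliefors version in 14–22%.

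**The case against.** The case on the other side is substantial, and much of it limits the point.

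- **Thin evidence.** Proportional spread is read from two arms of one cited study at one time, and the suture arm has no figures. This stands. If the arms do not differ, proportional spread also means equal SDs and the problem disappears. The sample size, however, is built on a difference of 1.08, which is where it appears.
- **Modest size.** The overall F test keeps its level when all arms are equal. Matrix against bipolar, the contrast used for planning, has a standard error off by only −8% to +7%. The 8% error is for an unadjusted comparison. With Tukey the figure is about 3.4%, and since that pair is then the only true null, familywise error stays below 5%. All this stands. The ANOVA sentence itself names no follow-up test, so applying Tukey there is an assumption.
- **The extremes are alternatives.** The 8% needs suture = matrix and the 1.8% needs suture = bipolar, so one trial cannot show both. Smaller errors in both directions can still occur together, as the midway row shows (0.91 and 1.14).
- **A condensed article.** The raw scale is inferred because no other is mentioned, and an unseen analysis plan might add detail. But the article does state the decision rule, and that rule tests shape and not variance. Further detail would have to override it.

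Two stronger readings are tempting. A reader might infer that the raw-scale ANOVA necessarily loses power. The protocol gives two means and two SDs but no distribution, and the answer reverses between lognormal and gamma data. A reader might also infer that the ANOVA is the likely route. Its probability depends on which version of the test is used and whether it is applied by arm, by time or overall, none of which is stated.

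**Conclusion.** The point holds as a correction of error bars. The gate for AMH ignores the assumption that the plan's own figures put in doubt. If the arms differ as planned, pairwise standard errors are wrong by −11% to +23%, and which pair is affected depends on where the suture arm falls.

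This rests on the two published SDs carrying over to this trial, on assumed suture values, on equal arm sizes and on a month-1 cross-section. It applies only when the ANOVA branch is entered. It does not show a general loss of power, and it does not undermine the overall F test under full equality. It is worth changing because the remedy is cheap and restores pairwise error to close to 5%.

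**What to change.** Under Data processing and analysis, remove the normality-test gate for AMH and prespecify one analysis that does not assume equal raw-scale variances. Either option would do:

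1. AMH on the natural-log scale, reported as ratios of geometric means with 95% confidence intervals. Under Sample size, the planning difference could then also be given as a ratio of means, 1.64/2.72 = 0.60.
2. AMH on the raw scale, in a model with arm-specific variances and unequal-variance pairwise comparisons.

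State in either case which multiple-comparison procedure follows.

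The cost is analysis wording only; no patients or visits are added, and 32 of 84 women had been randomized at the date given under Trial status. With option 1, results read as percent differences, values below the assay limit of 0.006 ng/mL need a substitution rule, and a few points of power may be lost if AMH is not close to lognormal. Option 2 keeps the original units and does not depend on lognormality.
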